## Abstract

**Background:**

Allergic rhinitis (AR) is an immune response of the nasal mucosa to airborne allergens and involves nasal congestion, watery nasal discharge, itching of the nose, and sneezing. The symptoms of allergic rhinitis may significantly affect a patient’s quality of life and can be associated with conditions such as fatigue, headache, cognitive impairment, and sleep disturbances. Various complementary and alternative medicine treatments have been used for this condition in clinical practice. The Ayurveda system of medicine is the most common complementary medicine system practiced in Sri Lanka. The aim of this study is to examine the efficacy and safety of a decoction used in traditional Ayurveda for allergic rhinitis and its ready- to-use freeze dried formulation in comparison to an antihistamine over a period of 4 weeks on relief of symptoms in allergic rhinitis.

**Study design:**

This is a three-arm, open-label, non-inferiority, randomized controlled clinical trial enrolling patients with AR. Tamalakyadi decoction containing 12 ingredients (TMD12), used in traditional Ayurveda and its freeze-dried formulation are the test products. The efficacy and safety of the two Ayurvedic dosage forms will be tested against the antihistamine loratadine. Patients with symptoms of AR will be allocated randomly into the three arms after a 1-week run-in period and the medications will be given orally for 28 days. Total Nasal symptom Score (TNSS) of the patients will be used as the primary efficacy endpoint. TNSS will be recorded and compared between the three arms prior to visit 1, at the end of 28 days, and end of the first and second months of follow-up. Symptom scores of daytime nasal symptoms, night time nasal symptoms, non-nasal symptoms and health-related quality of life questionnaire are used as secondary end points.

**Discussion:**

This clinical trial will be able to provide evidence-based scientific data on Ayurvedic dosage form, TMD12, and the freeze-dried formulation in the treatment of allergic rhinitis. This trial is expected to develop capacity to scientifically evaluate various Ayurvedic treatments that are claimed to have efficacy in treatment of various disease conditions.

**Trial registration:**

ISRCTN18149439 (6 May 2019).

## Background

Allergic rhinitis is an IgE-mediated immunological response of nasal mucosa to air-borne allergens and is characterized by nasal congestion, watery nasal discharge, itching of the nose, and sneezing. It is commonly defined as seasonal or perennial, depending upon whether symptoms are manifested at defined yearly intervals or throughout the year, respectively [1]. Allergic rhinitis is not life threatening, but for the patient it is an annoying and disturbing disease due to its chronicity and aggravation during exposure to allergic agents. Furthermore, allergic rhinitis is a considerable cause of widespread morbidity, medical treatment costs, reduced work productivity, and lost school days [2]. The symptoms of allergic rhinitis may significantly affect a patient’s quality of life and can be associated with conditions such as fatigue, headache, cognitive impairment, and sleep disturbances [3]. Appropriate management of allergic rhinitis is an important component in effective management of coexisting respiratory conditions such as asthma, sinusitis, and sleep apnea [4].

The World Allergy Organization (WAO) reports the prevalence of rhinitis symptoms in the International Study on Asthma and Allergies in Childhood (ISAAC) to vary between 0.8% and 14.9% in 6 to 7-year-olds and between 1.4% and 39.7% in 13 to 14-year-olds [5]. The reported prevalence in adults ranges from 8.7 to 24.1% in China and 11.4 to 22.7% in Turkey [6]. Also, in the USA, an estimated 20% of cases are seasonal allergic rhinitis and 40% of cases are perennial rhinitis [7].

In Sri Lanka, many people suffer from this condition. A survey of 6000 patients attending the OPD at the Teaching Hospital, Ragama, Sri Lanka, identified allergic manifestations in 8.8% of patients, and 22% of them had rhinitis [8]. Another survey conducted in Sri Lanka among schoolchildren in grade 5 from Western province, Sri Lanka, found symptoms of allergic rhinitis in 21.4% children with a statistically significant higher prevalence in boys [9]. The reason for this observation was not discussed in the paper.

Within Ayurveda and the Sri Lankan traditional medicine system, there are several potentially effective therapeutic methods of treatment for allergic rhinitis, which include internal as well as external treatment methods. Tamalakyadi decoction, which includes 12 ingredients (TMD12), is an herbal decoction used for treatment of allergic rhinitis in Ayurveda [10]. Decoctions are liquid dosage forms prepared freshly from herbs with a 24-h shelf life. Therefore, patients on treatments with decoctions need to prepare it daily, which causes difficulties in their busy lifestyles. Hence, this study plans to develop a ready-to-use dosage form, a freeze-dried powder of TMD12 packed into sachets, and investigate its efficacy and safety. No scientific studies have been published that have evaluated the efficacy and safety of TMD12 decoction either in allergic rhinitis. Therefore this study will evaluate the efficacy and safety of the traditional TMD12 decoction and its freeze-dried formulation in comparison to a non-sedating antihistamine loratadine used in an allopathic system in patients with symptoms of allergic rhinitis.

## Methods

### Study design

This is a three-arm, open-label non-inferiority randomized controlled clinical trial that will be conducted at the National Ayurveda Teaching Hospital in Colombo, Sri Lanka. TMD12, used in traditional Ayurveda, and its freeze-dried formulation will be the test products. The efficacy and safety of the two Ayurvedic dosage forms will be tested against the antihistamine loratadine. Patients with symptoms of AR will be allocated randomly into the three arms after a 1-week run-in period and the medications given orally for 28 days. This study protocol was developed as required by the Standard Protocol Items: Recommendations for Interventional Trials (SPIRIT) (Additional file 1).

Ethics approval has been obtained from Ethics Review Committee, Institute of Indigenous Medicine (ERCIIM), University of Colombo, Sri Lanka (ERC 18/76) and the Ethics Committee of the Faculty of Medicine, University of Colombo, Sri Lanka (EC-18-090). The trial was registered in the ISRCTN registry (Trial number ISRCTN18149439) (Additional file 2).

### Study setting

The study will be conducted in the Ayurveda Teaching Hospital, Borella, and the Institute of Indigenous Medicine (IIM) University of Colombo, Sri Lanka. The study subjects will be recruited from the patients with symptoms of allergic rhinitis who visit to the Outpatient Department (OPD) of Ayurveda Teaching Hospital and those who come, responding to a newspaper advertisement on trial recruitment.

### Participants

Patients will be selected from those seeking treatment for allergic rhinitis. Participation in this research project is voluntary. Patient recruitment is done by screening for eligibility criteria (inclusion and exclusion criteria). Eligible subjects will be randomly assigned to the TMD12 decoction group, TMD12 freeze-dried group (TMD12-FD) or the antihistamine, loratadine group.

### Inclusion and exclusion criteria

The inclusion criteria include (1) age group of 18–65 years at the time of enrollment, of either sex; (2) presence of two or more nasal symptoms (watery rhinorrhea, nasal obstruction, sneezing, and nasal itching); (3) Total Nasal Symptom Score (TNSS) > 6 (0 = no symptoms, 1 = mild symptoms, 2 = moderate symptoms, 3 = severe symptoms); (4) have given written, informed consent to participate in this study.

The exclusion criteria include: (1) Patients with deviated nasal septum/ nasal polyps/ nasal growth/ adenoids/ asthma; (2) Patients with impaired liver and kidney functions, anemia, and unstable cardiovascular conditions or cerebrovascular conditions; (3) currently or previously treated for any malignancy; (4) patients on steroid therapy; (5) already on treatment with TMD12 decoction or antihistamines; (6) pregnant or lactating mothers; (3) those who have known systemic disorders; (4) those who have any history of drug allergy to any of the investigational products; (7) illiterate patients without a literate relative/guardian who can explain the procedures and maintain the patient diary, (8) and any other patients who are considered unsuitable for recruitment by the investigators.

### Sample size

Sample size was calculated based on the primary outcome measurement of TNSS and as for a non-inferiority clinical trial. This study is designed to evaluate the comparative clinical efficacy and safety of two Ayurvedic dosage forms with the antihistamine loratadine, assuming non-inferiority-between the three interventions. Sample size was calculated as specified by Hampel et al. [11]. According to a previous study done among patients with allergic rhinitis using loratadine, clinically significant standardized effect sizes of TNSS are reported in the range of 0.57 to 0.67 [11]. Therefore, a standardized effect size of 0.5 was considered as the non-inferiority margin using the effect reported by Hampel and team.

Sample size was calculated for a significance level (**α**) of 5% and power of 80%. The sample size calculated using these values is 64 per group. With an expected dropout rate of 10%, minimum sample size was calculated as 70 for one arm.

### Recruitment

People who are interested in participating in this clinical study will be provided with a detailed Patient Information Leaflet (PIL) supplemented by verbal explanation of the study procedures. If the participants agree with the information given in PIL, the screening questionnaire will be completed. Informed written consent will be obtained from each participant by the investigators prior to initial interview. The activities in the initial interview will include complete history taking, physical examination, and hematological and biochemical investigations (IgE level, FBS, FBC, ESR, ALT/AST, serum creatinine, UFR). Diagnosis of allergic rhinitis will be made according to the Allergic Rhinitis and its Impact of Asthma (ARIA) criteria. Among them, the participants meeting the inclusion and exclusion criteria will be recruited for the study. All baseline assessment forms (Total Nasal Symptom Score, Quality of life questionnaire and allergic rhinitis symptom score) will be completed by the investigators. Patients will not be allowed to take any other medicines during the trial period. If they have to take any other medicine, they should inform the investigators and discontinue the trial.

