### Outcome measurements

#### Primary outcome

TNSS of the patients will be used as the primary efficacy endpoint, which has been previously used in allergic rhinitis clinical trials. The mean difference in TNSS will be compared between the three arms at baseline and at the end of 28 days, end of the first month of follow-up and second month of follow-up. The TNSS assesses the symptoms of watery rhinorrhea, nasal obstruction, sneezing, and nasal itching on a four-point scale. The total score range from 0 to 12 where 0 = absent symptoms (no sign/symptom evident), 1 = mild symptoms (signs/symptoms clearly present, but minimal awareness; easily tolerated), 2 = moderate symptoms (definite awareness of signs/symptoms that are bothersome but tolerable), 3 = severe symptoms (signs/symptoms that are hard to tolerate; causes interference with activities of daily living and/or sleep).

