#### Secondary outcomes

The following four symptom scores will be used as secondary end points.
Mean score of daytime nasal symptomsMean score of night time nasal symptomsMean score of non-nasal symptomsPatient’s self-rated symptom scores (daily rhinitis diary card) and allergic rhinitis grading symptoms will be used as secondary measures of the efficacy in the clinical trial. Such symptom scores will be collected on a weekly basis during the assessment period. The measurement of symptoms on a four-point rating scale with the following definitions will be used.
= absent symptoms (no signs/symptoms evident)= mild symptoms (signs/symptoms clearly present, but minimal awareness; easily tolerated)= moderate symptoms (definite awareness of signs/symptoms that are bothersome but tolerable)= severe symptoms (signs/symptoms that are hard to tolerate; causes interference with activities of daily living and/or sleep).Mean score of health-related quality of life score – Health-related quality of life is measured using allergic rhinitis symptoms at the baseline and end of the intervention (after 4 weeks, 1 month of follow-up, and 2 months of follow-up).

Changes in the serum IgE level and eosinophil count will be studied by comparing before and after treatment values. Procedures related to the study are shown in Table 2.

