## Method of data analysis

For primary and secondary outcome measures, the mean values at baseline and at the end of the study and the mean differences will be compared between the three arms using ANOVA (analysis of variance) or the non-parametric Kruskal–Wallis test, depending on the normality of the data. Within each treatment arm, the difference in primary and secondary outcome measures before and after the intervention period will be compared using paired-sample *t* test or non-parametric Wilcoxon signed-rank test, depending on the normality of the data. 95% confidence intervals will be calculated for all outcome measures that are normally distributed. Categorical variables will be compared between groups using the Chi-square test. Possible confounders will be adjusted using ANCOVA. Following adjustment for confounding using ANCOVA, adjusted mean values with confidence intervals will be calculated and reported. Statistical analysis will be performed using the SPSS Statistical Package program (ver. 18.0), and the level of significance will be established at α = 0.05. Missing data at outcome assessment will be replaced with the available latest values of the outcome measure. Intention-to-treat analysis will be performed for all efficacy outcomes and safety outcomes. In addition, per-protocol analysis will be performed for the efficacy outcomes by including only the patients completing the follow-up.

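### Patients who take another medicine must leave the trial, with no stated further scoring, so a treated relapse after day 28 is carried forward as maintained response or dropped from the month-1 and month-2 TNSS

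*Protocol article*

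**What the plan says.** Recruitment sets the rule in two sentences: "Patients will not be allowed to take any other medicines during the trial period", and then "If they have to take any other medicine, they should inform the investigators and discontinue the trial". The consequence is leaving the trial, not only stopping the study product. The rule does not separate rhinitis medicines from unrelated ones or treatment from follow-up, and it does not say whether outcomes are still collected afterwards. The term *trial period* is not defined.

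Study design limits treatment: "the medications given orally for 28 days". Primary outcome compares TNSS between arms at baseline and "at the end of 28 days, end of the first month of follow-up and second month of follow-up"; the abstract lists the same times. Secondary outcomes places quality of life at baseline and "after 4 weeks, 1 month of follow-up, and 2 months of follow-up".

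Method of data analysis fixes what happens to patients without a score: "Missing data at outcome assessment will be replaced with the available latest values of the outcome measure". It also states: "Intention-to-treat analysis will be performed for all efficacy outcomes and safety outcomes". The per-protocol efficacy analysis keeps only patients who complete follow-up.

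**The concern.** Patients enter with TNSS above 6 and a disease that the protocol itself calls chronic. For two months after day 28 they have no study product and, on the natural reading of the rule, may take nothing else. The patient whose symptoms return and who treats them is the one whose observation stops. The reason for the missing score is therefore tied to the outcome being measured.

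The same rule acts before day 28. One dose of an unrelated medicine ends participation before the main efficacy score. A patient given a medicine for an adverse event falls under it too, so the after-treatment laboratory tests may be lost.

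At stake is whether the month-1 and month-2 comparisons can show that benefit persisted or was lost. Scores that were never taken cannot be recovered at analysis.

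**Working it through.** **1. What happens to a patient who treats a relapse after day 28**

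| Step | Source | Result |
|---|---|---|
| Takes another medicine in follow-up | Recruitment | Discontinues the trial |
| Month-1 or month-2 TNSS is due | Primary outcome | No score; no provision to collect one |
| Intention-to-treat | Method of data analysis | Latest earlier TNSS substituted: day 28, or month 1 if the patient left after that visit |
| Per-protocol | Method of data analysis | Excluded, follow-up not completed |

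A patient who relapses and takes nothing stays in and is scored at the monthly visits. For a patient who leaves before day 28, the value carried forward is the baseline score if TNSS is taken only at the listed times. The study procedures table, which might show more, is not available.

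**2. The plan's own figure**

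Inputs from Sample size: margin 0.5 SD, α 5%, power 80%, 64 per group, 10% dropout, 70 per arm. With the normal approximation, n = 2(1.96 + 0.84)²/0.5² = 63. The t-based calculation gives 64 (power 0.8015), which reproduces the plan. This corresponds to two-sided 5% or one-sided 2.5%. For dropout, 64 × 1.1 = 70.4, which agrees with 70.

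**3. Hidden difference**

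The documents give no relapse or other-medicine rate, so everything here is assumed. Let p_T and p_L be the shares of a test arm and of loratadine that leave because they treat a relapse. Let R be their worsening, in SD, from the score carried forward. Suppose the arms have equal day-28 means, leavers had the same day-28 mean as the others, and patients who stay do not change. Then:

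- Difference in month-2 means had all been scored: (p_T − p_L) × R.
- Recorded difference: 0 in both analysis sets. Intention-to-treat inserts the day-28 value, and per-protocol averages only those who stayed.

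| p_T v p_L | R = 1 SD | R = 2 SD | Share of the 0.5 SD margin |
|---|---|---|---|
| 20% v 20% | 0 | 0 | 0 |
| 30% v 20% | 0.1 | 0.2 | 20 to 40% |
| 30% v 10% | 0.2 | 0.4 | 40 to 80% |
| 40% v 20% | 0.2 | 0.4 | 40 to 80% |
| 40% v 10% | 0.3 | 0.6 | 60 to 120% |

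Example: (0.30 − 0.10) × 1 = 0.2 and 0.2/0.5 = 40%; (0.30 − 0.10) × 2 = 0.4 and 0.4/0.5 = 80%. With p_T and p_L exchanged, the hidden difference has the opposite sign. At 20% in both arms no difference is hidden, but each arm's follow-up mean is understated by 0.2 to 0.4 SD.

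**4. Observed scores at month 2**

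With 70 per arm, observed n = 70 × (1 − share leaving), and power at the 0.5 SD margin is Φ(0.5√(n/2) − 1.96).

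| Share leaving (assumed, both arms) | Observed n per arm | Power |
|---|---|---|
| 10% | 63 | 80% |
| 20% | 56 | 75% |
| 30% | 49 | 70% |
| 40% | 42 | 63% |

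The 10% allowance covers dropout for every reason, not only other-medicine use.

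**The case against.** The strongest reply is that the analysis section already deals with leavers. A reader might infer that they vanish from the follow-up comparison and that the rule contradicts the intention-to-treat analysis. The documents do not support that: the missing-data sentence keeps them in the intention-to-treat mean, and only the per-protocol set drops them. This part of the reply stands. It does not remove the problem, because the value kept was measured before the relapse.

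Other stronger readings also fail:

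- **That the rule certainly covers follow-up.** It is the natural reading, since the primary outcome runs to month 2, but the term is undefined. The article is condensed, and its flow chart and procedures table are not shown.
- **That no score is taken after leaving.** This is inferred from the words on discontinuing; the article does not say it expressly.
- **That relapse as a whole goes unmeasured.** Untreated relapse is still scored.
- **That no missing-data method could help.** Patients are told to report other-medicine use, so disclosed use is known and could be counted as an unfavourable outcome. The plan as stated does not do this.
- **That the bias always favours non-inferiority.** It does so only if a test arm has more treated relapse.

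It is also fair to object that the rates in the working are invented, and that the exclusion of asthma, steroid therapy and known systemic disorders may keep other-medicine use low. The figures show what the rule could hide, not what it will hide. That patients may conceal use to avoid removal is possible, but nothing in the documents bears on it.

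**Conclusion.** The concern holds in this form: followed as written, the rule stops observation of randomised patients for an event related to the outcome. The stated analysis then treats a relapse that was treated after day 28 as maintained response (intention-to-treat) or leaves the patient out (per-protocol). Agreement between the two sets would give no reassurance, because both can miss the same difference.

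The size is unknown. At 30% against 10% leaving and a worsening of 1 to 2 SD, 0.2 to 0.4 SD is hidden. With equal shares and equal worsening no difference between arms is hidden, and at 40% against 10% the amount can exceed the margin. The margin serves here only as a yardstick for the follow-up visits. The calculation assumes equal day-28 means, leavers typical of their arm at day 28, and stable scores in those who stay. R is the worsening that would stand at the visit; if the other medicine relieves symptoms, the score actually observed would be lower, and the share taking it then carries the information.

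That the follow-up months are affected rests on the natural reading of an undefined term. The loss before day 28 does not depend on that reading.

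**What to change.** Reconcile Recruitment, Primary outcome and Method of data analysis:

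1. State whether the trial period includes the two follow-up months.
2. Separate stopping the study product from leaving the trial. After other-medicine use, scheduled TNSS, quality-of-life and safety assessments continue to month 2 unless consent is withdrawn.
3. Ask about other medicines at each visit and in the existing patient diary, and record name, dates and reason.
4. Do not replace a score after such use by an earlier value when the score can be observed.
5. Report by arm the share taking a rhinitis medicine after day 28, beside the month-1 and month-2 TNSS.

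Which medicines are allowed, and which, if any, require the study product to be stopped, is for the sponsor to decide.

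The cost is a short text change, a diary line and a case record form field, with no new visits. Recruitment is in progress, so it is an amendment that goes to the ethics committees and the registry. Patients who have already left may not be recoverable. Some follow-up scores will be measured under other medicines and must be read beside the recorded use.

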### Baseline assessment

Nasal symptoms (watery rhinorrhea, nasal obstruction, sneezing, nasal itching), non-nasal symptoms, HRQoL, hematological and biochemical investigations (IgE level, FBS, FBC, ESR, ALT/AST, serum creatinine, UFR) will be assessed at baseline.

